#### Criteria for discontinuing or modifying allocated interventions {11b}

Modification of the allocated intervention will be based on the planned interim analysis. Outcome of the interim analysis will lead to making decision regarding selection of higher C-IVIG dose in case of currently selected 0.15 g/kg dose not found efficacious. The higher dose of C-IVIG will be selected from the dosage investigated in previous phase I/II clinical trial [11]. The C-IVIG infusion will be discontinued if any serious adverse event occurs or discontinued on patient request and the patient will be excluded from the study.

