#### Intervention description {11a}

Intervention group will receive a single dose of 0.15 g/kg body weight C-IVIG along with standard care. Control arm will receive standard hospital care only. The dose will be administered intravenously with a flow rate of 20 ml/h in the first hour and 25 ml/h till the dosage end. Standard hospital care includes airway support, anti-viral medication, antibiotics, fluid resuscitation, hemodynamic support, steroids, painkillers, and anti-pyretic. Standard of care will ensure blinding because as part of the usual hospital care severe COVID-19 patients is given multiple infusion, and hence, it will not be possible for patients in intervention group and control group to discriminate between standard of care and C-IVIG infusion.

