#### Outcomes {12}

Primary outcome:28-day mortality [time frame: 28 days]All-cause mortality of participants will be monitored for 28 days to assess the safety and efficacy of C-IVIG

Secondary outcomes:Immediate (within 24 h) or serious adverse events (throughout the hospital stay) [time frame: 28 days]Clinical status according to 7 category ordinal Scale [time frame: 28 days (till hospital stay)Not hospitalized and no limitations of activitiesNot hospitalized, with limitation of activities, home oxygen requirement, or bothHospitalized, not requiring supplemental oxygenHospitalized, requiring any supplemental oxygenHospitalized, requiring noninvasive ventilation or use of high-flow oxygen devicesHospitalized, receiving invasive mechanical ventilationDeathChange in Horowitz index (PaO_2_/FiO_2_ ratio use to assess lung function) during hospital stay [time frame: 28 days]Change in C-reactive protein (CRP) levels, radiological findings, IL-6 level, and anti-SARS-CoV-2 antibody levels [time frame: 5 days]

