### Statistical methods

#### Statistical methods for primary and secondary outcomes {20a}

Patients will be randomized at a ratio of 2:1 to receive either C-IVIG with standard of care or standard of care only. The data to be analyzed will be blinded using the SPSS software 24.0. All randomized study participants will be included in the intention-to-treat population and all participants completing the study period will be analyzed (complete case analysis). Normality of continuous data will be checked by the Shapiro-Wilk test, and parametric or non-parametric tests will be applied accordingly. Continuous variables will be presented as mean (± SD) or median (interquartile range), and categorical variables will be presented as percentages. In the primary analysis strategy, we will use the Kaplan–Meier curve (Breslow test) that compares the time to reach the primary end point in the trial groups. Hypothesis testing of outcomes for the assessment of safety and efficacy parameters will be conducted by Mann-Whitney *U* test or independent *t*-test. Categorical data will be compared with chi-square test, and value of the two-sided Fisher exact test will be recorded. An estimate of the relative risk and 95% confidence interval will also be reported. Hypothesis testing will be conducted at a significance level of 0.05.

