#### Methods in analysis to handle protocol non-adherence and any statistical methods to handle missing data {20c}

To handle the missing data multiple imputation will be used or complete case analysis will be used. The primary analysis will use the intention-to-treat principle.

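### Patients whose C-IVIG infusion is stopped are excluded from the study: only one arm can trigger this rule, and it contradicts the intention-to-treat analysis of 28-day mortality

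*Protocol article*

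**What the plan says.** All references are to the protocol article.

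- **Criteria for discontinuing or modifying allocated interventions {11b}:** on C-IVIG treatment, the rule reads: "infusion will be discontinued if any serious adverse event occurs or discontinued on patient request and the patient will be excluded from the study". There are two triggers, a serious adverse event of any cause and a patient's request. Both lead to exclusion.
- **Intervention description {11a}:** "Control arm will receive standard hospital care only".
- **Outcomes {12}:** the primary outcome is 28-day mortality. "All-cause mortality of participants will be monitored for 28 days to assess the safety and efficacy of C-IVIG".
- **Statistical methods {20a}:** randomised participants are to be "included in the intention-to-treat population and all participants completing the study period will be analyzed (complete case analysis").
- **Protocol non-adherence and missing data {20c}:** "The primary analysis will use the intention-to-treat principle". The same section says: "To handle the missing data multiple imputation will be used or complete case analysis will be used".
- **Participant retention {18b}:** data gathered before loss to follow-up are used. After withdrawal for an adverse event, the event is followed until it resolves. Discharged participants are followed by telephone.
- **Adverse event reporting {22}:** adverse and serious adverse events are recorded from enrolment to day 28.

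**The concern.** Stopping a treatment and leaving a trial are different things, and {11b} joins them. A patient who has a serious event while C-IVIG is running is removed after randomisation, for a reason likely to be related to prognosis. A control patient with the same event at the same time stays in, because there is no C-IVIG infusion to stop. The randomised comparison of 28-day mortality is then no longer between the groups that were randomised.

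This is a rule of conduct. If follow-up ends at exclusion, day-28 status is never collected, and no later analysis plan can recover it. Mortality is also reviewed at the interim analyses, and the Discussion lists significantly higher mortality in the intervention group as a ground for early termination. A gap in mortality follow-up confined to that group would affect this review too.

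**Working it through.** **1. Can the passages be followed together?** No figure in the protocol belongs to this point, so the first check is of the text.

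- {11b} takes the patient out of the study; {20c} analyses by intention to treat. Both cannot hold for the same patient.
- {20a} puts every randomised participant in the intention-to-treat population, but the same sentence limits analysis to those who complete the study period. An excluded patient is not a completer and drops out.
- {20c} leaves multiple imputation and complete-case analysis as alternatives, so imputation is not assured.
- {18b} continues follow-up of the adverse event. It does not say that day-28 vital status is collected or analysed.
- In the planned Kaplan–Meier analysis, a patient who survives the event and is then excluded would at best be censored at that time. The reason for censoring is a prognostic event, so the censoring is informative.

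**2. How long can the rule be triggered?** Inputs: 0.15 g/kg, 5% solution (0.05 g/ml), 20 ml in the first hour, then 25 ml/h ({6b}, {11a}). Body weight is an assumption.

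- Volume = 0.15 × weight / 0.05. At 70 kg: 210 ml.
- Duration = 1 + (volume − 20)/25. At 70 kg: 1 + 190/25 = 8.6 h.
- At 50 kg: 150 ml, 6.2 h. At 90 kg: 270 ml, 11.0 h.

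**3. What could it do to the mortality comparison?** The protocol gives neither the share excluded, *s*, nor their mortality, *d*; both are assumptions. Other inputs: 206 and 103 patients; two-sided 0.05 ({20a}); no true effect; no other losses. The common mortality *p* is set at each planning value in the sample size section: 60% (control survival 40%) and 25% (intervention survival 75%).

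- Observed C-IVIG mortality: *r* = (*p* − *s·d*)/(1 − *s*).
- Standard error: SE = √[*p*(1−*p*)/103 + *r*(1−*r*)/*n*], with *n* = 206(1 − *s*), rounded.
- Chance of a false favourable result: Φ((*p* − *r*)/SE − 1.96).

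Worked case, *p* = 0.60, *s* = 0.10, *d* = 1: *r* = 0.50/0.90 = 0.556; *n* = 185; SE = √(0.2400/103 + 0.2469/185) = 0.0605; Φ(0.0444/0.0605 − 1.96) = 11.0%.

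All excluded patients die (*d* = 1):

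| Excluded share of C-IVIG arm | Observed mortality, *p* = 60% | False favourable | Observed mortality, *p* = 25% | False favourable |
|---|---|---|---|---|
| 0% | 60.0% | 2.5% | 25.0% | 2.5% |
| 2% (about 4) | 59.2% | 3.4% | 23.5% | 4.8% |
| 5% (about 10) | 57.9% | 5.4% | 21.1% | 11.6% |
| 10% (about 21) | 55.6% | 11.0% | 16.7% | 37.6% |

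If 80% of the excluded die, 5% exclusion gives 3.7% (*p* = 60%) and 8.0% (*p* = 25%).

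**4. Is the direction certain?** No. If *d* = *p*, then *r* = *p* and there is no bias. If *d* is below *p*, the bias runs against C-IVIG: with *p* = 0.60, *s* = 0.05 and *d* = 0, *r* = 0.60/0.95 = 63.2%.

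The calculation compares proportions by a normal approximation. It is not a simulation of the planned Breslow test.

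**The case against.** The best defence is that exclusion here means withdrawal from treatment. {20a} counts all randomised participants in the intention-to-treat population, {18b} uses data up to loss to follow-up, and {20c} allows imputation. A death during the infusion is already an observed primary event. This shows that complete deletion is only one reading. It does not remove the problem, because the words say the study, not the treatment, and the completer wording in {20a} points to dropping these patients.

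The number affected may also be small. The window is a matter of hours, patients already on non-invasive or invasive ventilation are ineligible, and {6b} reports no drug-related adverse events. This stands. The 10% rows show what the rule could do and are not a forecast.

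Two stronger readings are tempting, and the document supports neither.

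- *The rule erases the serious adverse events that the interim analyses are meant to find.* {22} records these events to day 28, {18b} follows them after withdrawal, and {21b} and the Discussion have them reviewed at interim. Nothing says that a recorded event is deleted. The main loss is later mortality and clinical status.
- *The bias must favour C-IVIG.* Patients who stop on request need not have a worse prognosis, so their exclusion could act in either direction.

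**Conclusion.** The point holds as a contradiction in the text. {11b} prescribes a post-randomisation exclusion that only the C-IVIG arm can incur, which cannot stand beside the intention-to-treat primary analysis in {20a} and {20c}. No other section secures day-28 vital status for these patients.

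The size cannot be derived from the document. If excluded patients die at the arm's average rate, there is no bias. If all of them die and there is no true effect, excluding 2% to 10% of the C-IVIG arm raises the false favourable chance from 2.5% to between 3.4% and 11.0% at 60% mortality, and to between 4.8% and 37.6% at 25% mortality. These figures rest on assumed shares and mortality and on full removal from the analysis. Bias towards C-IVIG is the expected direction for exclusions after serious adverse events, provided those patients die more often than the rest. It is not established for exclusions on request.

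**What to change.** Leave the rule on when to stop the infusion as it is; that is a clinical matter. Make two changes of wording.

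1. In {11b}, replace the closing clause on exclusion with: *the patient remains in the study, is followed to day 28 for vital status and adverse events, and is analysed in the randomised arm; only withdrawal of consent to follow-up ends data collection.*
2. In {20a}, state that the primary analysis includes all randomised participants as randomised, and that complete-case analysis is a sensitivity analysis only. Bring the either/or on missing data in {20c} into line. Without this second change, the completer wording could still drop patients who lack complete data.

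The cost is a short amendment. Telephone follow-up after discharge is already planned in {18b}, and the denominators stay at 206 and 103. The small downside is that the efficacy figures may look slightly less favourable.

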#### Strategies to improve adherence to interventions {11c}

It is not applicable because the drug will be given as a single dose intravenously by respective healthcare professionals.

#### Relevant concomitant care permitted or prohibited during the trial {11d}

Standard hospital care including all concomitant care and interventions are permitted.

#### Provisions for post-trial care {30}

No provisions are made for ancillary and post-trial care.

#### Outcomes {12}

Primary outcome:28-day mortality [time frame: 28 days]All-cause mortality of participants will be monitored for 28 days to assess the safety and efficacy of C-IVIG

Secondary outcomes:Immediate (within 24 h) or serious adverse events (throughout the hospital stay) [time frame: 28 days]Clinical status according to 7 category ordinal Scale [time frame: 28 days (till hospital stay)Not hospitalized and no limitations of activitiesNot hospitalized, with limitation of activities, home oxygen requirement, or bothHospitalized, not requiring supplemental oxygenHospitalized, requiring any supplemental oxygenHospitalized, requiring noninvasive ventilation or use of high-flow oxygen devicesHospitalized, receiving invasive mechanical ventilationDeathChange in Horowitz index (PaO_2_/FiO_2_ ratio use to assess lung function) during hospital stay [time frame: 28 days]Change in C-reactive protein (CRP) levels, radiological findings, IL-6 level, and anti-SARS-CoV-2 antibody levels [time frame: 5 days]

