### Trial design {8}

This is an adaptive, phase II/III, multi-center, randomized controlled, single-blinded superiority trial with parallel group design to assess the safety and efficacy of single dose of C-IVIG in patients with symptoms of severe COVID-19. Eligible participants will be randomly assigned in 2:1 ratio (206 tests: 103 controls) by block randomization method to receive C-IVIG plus standard of care (intervention group) or only standard of care (control group). The adaptive study design refers to adapting the strategy of trial based on interim analysis at three particular time points [12]. Outcome of the interim analysis will lead to making decision for terminating trial in case of serious adverse events or selecting a higher C-IVIG dose regime in case selected dose of C-IVIG (0.15g/Kg) not found efficacious. A flow chart of the trial design is shown in Fig. 1.

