#### Plans to promote participant retention and complete follow-up {18b}

Designated personnel from the trial staff will be appointed to ensure the participant retention and complete follow-up during the participant’s hospital stay and after discharge as well. After a participant’s hospital discharge, participants will be followed on call. The participant can withdraw from the trial at any point. The decision will be communicated with the study investigator; the clinical research associate should be explaining the importance of staying in the trial for the full duration of follow-up. For withdrawal, there is a form in CRF that will be filled by the clinical research associate with reasoning why the participant is withdrawing from the trial. If the participant will be lost to follow-up, the data that will be collected till the time of loss to follow-up will be assessed and used in the analysis.

If the patient will withdraw due to AEs, the clinical associate or the treating physicians will closely monitor the follow-up of AEs until the participants return to the baseline state or the participant condition returns to normal. Then the AEs will be reported to the study investigators.

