#### Plans for collection, laboratory evaluation and storage of biological specimens for genetic or molecular analysis in this trial/future use {33}

Biological specimens of hospitalized patients will be collected and sent to the laboratory by on-duty staff according to the given schedule and as recommended by the treating physician. Discharged patients will be contacted via phone call and their samples will be collected by the study investigators. All samples will ultimately be sent to the laboratory or at predetermined storage conditions.

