### Composition of the data monitoring committee, its role and reporting structure {21a}

#### Adverse event reporting and harms {22}

Adverse events (AE) and serious adverse events (SE) will be observed and reported from the time of patient’s enrollment in the study till the outcome day, i.e., 28 days. AE/SE will be reported in the clinical research forms which include the time of the AE/SE medications, severity, duration of the AE, and the outcomes after AE. The relevant information of adverse events, after investigating if it is drug related or not, will be reported within 24 h to the principal investigator and to the National Drug Authorities.

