## Discussion

This phase II/III clinical trial is an adaptive, randomized controlled, multi-center, single-blinded superiority trial of SARS-CoV-2 specific polyclonal IVIG (C-IVIG) versus standard of care for patients hospitalized with severe COVID-19. Single dose of C-IVIG in combination with the standard of care was found to be both safe and efficacious in our previous clinical trial phase I/II while increasing the survival rate and reducing the risk of disease progression [13]. There were no significant changes observed when different doses of C-IVIG were compared in the phase I/II; however, it was found that C-IVIG dosage of 0.15 g/kg have significantly improved the therapeutic response in severe COVID-19 patients. These results warrant the phase II/III clinical trial study of C-IVIG, in order to evaluate its safety and efficacy in large sample size by comparing outcomes (28-mortality, hospital stay and drug-related adverse events) of C-IVIG along with SOC in intervention group and SOC only in comparator group provided during the hospital stay.

Study participant selection for this study is based on the results of our previous clinical trial where severe patients had 100% survivability and early hospital discharge than critical patients and comparator group. We evaluated that hospital stay, reliance on mechanical ventilation, and burden on hospital could be reduced if C-IVIG is administered to the severe COVID-19 patients by delaying the disease progression.

This is an adaptive clinical trial to investigate the risk-benefit analysis of C-IVIG administration for severe COVID-19 at first and second interim of the study. Major outcome variables to be assessed for interim analysis are adverse events, 28-day mortality, and change in clinical status of the patients. Fate of this clinical trial is based on whether the C-IVIG is safe and efficacious. If the treatment modality is found to be safe but not efficacious as compare to comparator group, we might select different dosage of C-IVIG for further study participants; if interim analysis indicate association of serious adverse events with administration of C-IVIG or with significant high mortality ratio in intervention group than comparator group or if incidence rate of COVID-19 is low till the study completion date, then this clinical trial would be early terminated due to aforementioned reasons.

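### The serious adverse event outcome is limited to the hospital stay although events are collected to day 28, so post-discharge events drop out and time at risk can differ by arm

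*Protocol article*

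**What the plan says.** All references are to the protocol article.

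- **Outcomes {12}** lists as a secondary outcome "Immediate (within 24 h) or serious adverse events (throughout the hospital stay) [time frame: 28 days". The hospital stay is in the parenthesis and 28 days is in the bracket.
- **Adverse event reporting and harms {22}** has adverse and serious adverse events observed and reported from "enrollment in the study till the outcome day, i.e., 28 days". Discharge is not mentioned as an end point.
- **Participant retention and follow-up {18b}** says that after discharge "participants will be followed on call".
- **Discussion** states the expectation that "hospital stay, reliance on mechanical ventilation, and burden on hospital could be reduced if C-IVIG is administered", and reports earlier discharge of severe patients than of the comparator group in the phase I/II trial.
- **Blinding {17a}** blinds participants only.
- **Statistical methods {20a}** says "Categorical data will be compared with chi-square test" and "An estimate of the relative risk and 95% confidence interval will also be reported".
- **Sample size {14}** assumes survival of 75% on C-IVIG and 40% in control.

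**The concern.** The outcome definition and the harms section give serious adverse events two different windows. If the outcome follows {12}, a serious event after discharge but before day 28 is recorded on the case report form and then left out of the between-arm comparison.

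The window also ends at an event that happens after randomisation and may depend on treatment. If stays differ by arm, patients in the two arms are observed for different lengths of time. A comparison of simple proportions then mixes the rate of serious events with the time available to observe them. Because only participants are blinded, staff who know the allocation can influence when counting stops. What is at stake is the interpretation of a named safety outcome: an apparent difference may be produced, or a real one masked, by discharge timing.

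**Working it through.** **1. The two windows.** In {12} the parenthesis limits serious events to the stay and the bracket gives 28 days. If the bracket alone were the window, the parenthesis would have no function, so the natural reading is the stay with a 28-day cap. {22} runs to day 28 with no reference to discharge. The two windows differ for every patient discharged alive before day 28.

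**2. Effect of unequal stays, ignoring death.** The document gives no stays and no event rates, so every input here is assumed: the same serious-event hazard in both arms, a control stay of 12 days, and a C-IVIG stay of 11, 10 or 8 days.

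*Constant hazard* h = 0.01 per day; risk = 1 − exp(−h·d).
- 8 d: 7.69%; 10 d: 9.52%; 11 d: 10.42%; 12 d: 11.31%; 28 d: 24.42%.
- Apparent relative risk against 12 d: 10.42/11.31 = 0.92; 9.52/11.31 = 0.84; 7.69/11.31 = 0.68.

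*Falling hazard*, halving every 7 days, with the same 28-day cumulative hazard of 0.28.
- 8 d: 15.08%; 10 d: 17.11%; 11 d: 17.98%; 12 d: 18.75%; 28 d: 24.42%.
- Apparent relative risk: 0.96, 0.91 and 0.80 for 11, 10 and 8 days.

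Without death, a day-28 window would give 24.42% in both arms, a ratio of 1.00.

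**3. Adding death as a competing event.** The only outcome rates in the document are the survival assumptions in {14}: 75% on C-IVIG and 40% in control. Keep the non-fatal serious-event hazard at 0.01 per day in both arms and let m be the death hazard. The risk of a serious event by day d is h/(h+m) × [1 − exp(−(h+m)·d)].

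*Deaths spread evenly over 28 days:* m = −ln(0.75)/28 = 0.01027 on C-IVIG and −ln(0.40)/28 = 0.03272 in control.
- In hospital, 10 versus 12 d: 9.05% versus 9.39%, relative risk 0.96.
- To day 28: 21.37% versus 16.33%, relative risk 1.31.

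*All deaths before discharge:* m = −ln(0.75)/10 = 0.02877 on C-IVIG and −ln(0.40)/12 = 0.07636 in control.
- In hospital, 10 versus 12 d: 8.29% versus 7.47%, relative risk 1.11.
- In hospital, 8 versus 12 d (C-IVIG m = −ln(0.75)/8 = 0.03596): 6.69% versus 7.47%, relative risk 0.90.
- To day 28, 10 versus 12 d. Event-free survivors at discharge are 0.75 × exp(−0.10) = 67.9% and 0.40 × exp(−0.12) = 35.5%. They continue at h for 18 and 16 days, which gives 19.47% versus 12.72%, relative risk 1.53.

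**4. Reading.** With no true difference in the serious-event hazard, the in-hospital ratio lies on either side of 1 depending on assumptions that the document does not settle. The day-28 window removes the dependence on discharge. It does not return 1.00 once mortality differs, because control patients who die early have less time in which to have a non-fatal serious event.

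**The case against.** The strongest reply is that this is loose wording in a condensed article. The item in {12} itself carries a 28-day time frame, the Abstract says patients are followed for 28 days for primary and secondary outcomes, and {22} is the dedicated harms section. On that view the authors may always have meant day 28. The assessment schedule in Table 1 is not reproduced in the text at hand, so it cannot settle the matter. This stands in part: the text is not clear evidence of a decision to discard later events. But the two sections still state different windows for a named outcome, and the same edit resolves it on either reading.

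Three stronger readings are tempting and are not supported.

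- *The window makes C-IVIG look safer.* A reader might infer this from the expected shorter stays. The sample-size section also expects far more control deaths, and death ends time at risk too, so the direction is open.
- *The interim stopping rule is compromised.* Serious events can lead to "terminating trial in case of serious adverse events", but neither that section, nor {21b}, nor the Discussion limits the events considered there to the hospital stay. The limit appears only in {12}.
- *All later events will be known.* The statement that "Discharged patients will be contacted via phone call and their samples will be collected by the study investigators" concerns specimens, and {18b} describes post-discharge contact only in general terms. Ascertainment after discharge may be incomplete.

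The constant-hazard figures also assume that a discharged patient keeps an inpatient's risk. The falling-hazard case is more plausible and gives smaller distortions.

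**Conclusion.** The point holds as an internal inconsistency with a real analytic consequence. As written, {12} excludes post-discharge serious events that {22} already collects, and it ends counting at a post-randomisation event that treatment may change and unblinded staff can influence. The comparison in {20a} does not allow for the resulting difference in time at risk.

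No trial-specific size can be given. Under the assumed inputs above, with no true difference, the in-hospital relative risk runs from 0.68 (8 versus 12 days, constant hazard, no deaths) to 1.11 (10 versus 12 days, all deaths before discharge). These figures show only that the window can move the result, not by how much or in which direction here. The primary outcome, 28-day all-cause mortality, is unaffected and remains a safety measure. Importance is low to moderate.

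**What to change.** In {12}, replace the hospital-stay parenthesis for serious adverse events with *from randomisation to day 28, regardless of discharge*, which brings it into line with the day-28 end point in {22}. Leave the 24-hour definition of immediate events as it is. Use the same serious-event definition at the interim reviews in {21b}, counting to the data cut or day 28, whichever comes first.

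Because a fixed window does not remove the competing effect of death, present serious events beside 28-day mortality, for example with an additional comparison in which death counts as part of the event.

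The cost is small: one phrase in {12} and matching wording in {21b}. Collection to day 28 and telephone follow-up are already planned, so no new visits are needed. The downside is that events after discharge depend on phone reports and may be less complete than those in hospital.

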**Methods:**

This is a phase II/III, adaptive, multi-center, single-blinded, randomized controlled superiority trial of SARS-CoV-2 specific polyclonal IVIG (C-IVIG). Patients fulfilling the eligibility criteria will be block-randomized using a sealed envelope system to receive either 0.15 g/Kg C-IVIG with standard of care (SOC) or standard of care alone in 2:1 ratio. The patients will be followed-up for 28 days to assess the primary and secondary outcomes.

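### The hospital-stay qualifiers on the SAE and ordinal-scale outcomes conflict with the 28-day window stated elsewhere; if applied, they could tilt the safety comparison towards C-IVIG

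*Protocol article*

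**What the plan says.** Outcomes {12} lists two secondary outcomes with a double time frame:

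- Safety: immediate events, within 24 h, or "serious adverse events (throughout the hospital stay", under a 28-day label.
- Clinical status: "Clinical status according to 7 category ordinal Scale [time frame: 28 days (till hospital stay". Categories 1 and 2 of this scale are both states outside hospital, with and without limitation or home oxygen; category 7 is death.

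Other parts of the article give one window. Adverse event reporting and harms {22} states that adverse and serious adverse events "will be observed and reported from the time of patient’s enrollment in the study till the outcome day, i.e., 28 days". The Methods paragraph of the abstract says: "The patients will be followed-up for 28 days to assess the primary and secondary outcomes". Under participant retention {18b}, after discharge "participants will be followed on call".

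Three other sections bear on the consequence. The Discussion reports earlier discharge of severe patients in the previous trial and suggests that C-IVIG could reduce time in hospital. It also names adverse events and change in clinical status among the main interim variables. Statistical methods {20a} plans chi-square or Fisher tests and a relative risk for categorical data, with no allowance for time at risk.

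**The concern.** Take a patient discharged on day 9 who has an SAE on day 20. Under {22} the event is observed and reported. Under the qualifier in {12} it is not part of the safety outcome. Two analysts working from the same article could count different events.

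Length of stay may itself be changed by treatment. A window that closes at discharge closes earlier in the arm that goes home earlier, and a plain comparison of proportions then credits that arm with fewer events. Here the error would favour the test product, on the main safety measure, and it would reach the interim decisions on stopping the trial or changing the dose.

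For the ordinal scale, a window ending at discharge can at best assign category 1 or 2 at the moment of leaving. Later decline, readmission or a new need for home oxygen would not be scored.

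**Working it through.** **Reading the sections together**

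| Item | Outcomes {12} | Elsewhere |
|---|---|---|
| SAEs | labelled 28 days, qualified by hospital stay | enrolment to day 28 ({22}) |
| Ordinal scale | labelled 28 days, qualified by hospital stay | 28-day follow-up for secondary outcomes (abstract); calls after discharge ({18b}); categories 1 and 2 lie outside hospital ({12} itself) |

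The 28-day label does not settle the matter. Read with its qualifier, it means the stay, capped at 28 days. Read without it, the qualifier has no function.

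**Size of the possible bias**

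The documents give no SAE rate and no length of stay, so there is no figure of the plan to reproduce. All inputs below are assumptions: a daily SAE hazard h that is equal in both arms, and one common stay per arm.

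Proportion with a counted SAE = 1 − exp(−h × days observed).

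With h = 0.01 per day and stays of 8 days (C-IVIG) v 12 days (control):

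- C-IVIG: 1 − exp(−0.08) = 7.7%
- Control: 1 − exp(−0.12) = 11.3%
- Relative risk: 0.0769 / 0.1131 = 0.68
- Fixed 28-day window: 1 − exp(−0.28) = 24.4% in both arms, relative risk 1.00

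Range over other assumed values (C-IVIG v control):

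| h per day | 7 v 10 days | 8 v 14 days | 10 v 10 days | 28 days, both arms |
|---|---|---|---|---|
| 0.005 | 3.4% v 4.9%, RR 0.71 | 3.9% v 6.8%, RR 0.58 | RR 1.00 | 13.1%, RR 1.00 |
| 0.01 | 6.8% v 9.5%, RR 0.71 | 7.7% v 13.1%, RR 0.59 | RR 1.00 | 24.4%, RR 1.00 |
| 0.02 | 13.1% v 18.1%, RR 0.72 | 14.8% v 24.4%, RR 0.61 | RR 1.00 | 42.9%, RR 1.00 |

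The relative risk depends mostly on the ratio of the stays and little on the hazard.

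**If the hazard falls with recovery**

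Keep stays of 8 v 12 days, with h = 0.01 to day 8 and 0.005 afterwards in both arms. C-IVIG stays at 7.7%. Control becomes 1 − exp(−(0.08 + 4 × 0.005)) = 1 − exp(−0.10) = 9.5%. The relative risk is 0.0769 / 0.0952 = 0.81. If the hazard were zero after day 8, both arms would show 7.7% and the relative risk would be 1.00.

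**The case against.** The best defence is that the article as a whole points to 28 days. Both outcomes carry that label, the abstract and {22} repeat it, and {18b} provides contact after discharge. On this view the brackets are loose wording, and SAEs after discharge are collected in any case. This has force. A reader might infer from {12} that SAEs are counted only in hospital, and the documents do not support that flatly. What stays open is whether events collected after discharge enter the secondary outcome.

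The size can also be challenged. The stays and hazards are invented, and patients are discharged because they have improved, so a hazard that stays constant after discharge probably overstates the loss. The Discussion says only that stay could be shorter. All-cause death is the primary outcome to day 28, so fatal events are protected whatever the discharge date. These points stand as limits on the magnitude; they do not remove the conflict.

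Categories 1 and 2 could be assigned at discharge, so they are not strictly unusable. That still leaves everything after discharge unscored.

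Three further inferences are tempting but unsupported:

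- That there is no common day on which patients are compared. The assessment schedule (Table 1) is not shown and may fix the days.
- That immediate events lack a start point in controls. Interim analyses {21b} ties these events to drug administration. Timing them from randomisation could cut off reactions to a delayed infusion.
- That the rank test in {20a} is wrong for an ordinal scale. No error in it is shown, and a proportional-odds model would be a preference.

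**Conclusion.** The point holds as a conflict in stated outcome definitions, with a plausible direction of bias. It is not detail left to another document: {12} states a restriction that {22}, the abstract and the scale's own categories contradict.

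Applying the restriction loses SAEs after discharge from the safety outcome in both arms. It biases the relative risk only if stay differs by arm, which the Discussion expects but the documents do not quantify. Under equal constant hazards of 0.005 to 0.02 per day and the unequal stays tried, the counted relative risk is 0.58 to 0.72 with no true difference. A falling hazard moves it towards 1.00, and equal stays give 1.00. These figures show what the wording can do; they do not predict this trial's result. The outcomes are secondary, but one is the main safety measure and both feed the interim decisions, so the wording should be corrected before it is applied.

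**What to change.** Amend Outcomes {12} as follows:

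- Delete the hospital-stay qualifiers from both outcomes.
- Define the SAE outcome as events from randomisation to day 28 in both arms, whether or not the patient has been discharged. Reporting under {22} already covers this period.
- Score the ordinal scale for all randomised patients through day 28, including day 28 itself. Use the calls in {18b} after discharge, and score death as category 7.
- Check that the assessment schedule in Table 1 agrees.

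The definition of immediate events and the choice of test need no change for this purpose.

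The cost is an amendment to the outcome wording and a few scripted questions on calls already planned. The calls become slightly longer. Reported SAE rates will be higher than with an in-hospital count, because events after discharge are included.
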